## 3. Results and Proposed Data Analyses

The primary outcomes of the proposed study will include subjective feasibility outcomes per a self-report from the participant, as well as objective feasibility outcomes reported by the experimenter. To determine if the participant is able to tolerate the VR, we will use the Simulation Sickness Questionnaire (SSQ). The SSQ will evaluate tolerability by measuring side effects of VR such as fatigue, dizziness, and headache on a four-point scale (none, slight, moderate, severe) [36]. Further assessments of feasibility will include fNIRS signal quality, as well as preliminary measures of cognitive and motor performance. These outcomes will produce descriptive and qualitative results related to feasibility assessment. A summary of these results, including specific questions assessing feasibility, can be found in Table 2. Below are further descriptions of the neural results that will be obtained via the fNIRS apparatus and the motor performance results yielded by the VR controllers.

### 3.1. fNIRS Results

The preliminary fNIRS data results, and the primary outcome of feasibility in this current paper, will be a simple assessment of the signal quality of the raw data (Table 2). Prior to data processing, this will involve a visual inspection of which channels yielded high-quality signals; i.e., channels with a visible and consistent cardiac pulsation, which is indicative of an appropriate hemodynamic response [60], and minimal visible noise due to movement or other artifacts. Then, data will be processed using Homer3 (v1.87.0) via MATLAB (R2024b), which will include pruning noisy signals, correcting the signal for motion artifact, converting the raw data to optical density, applying a bandpass filter to remove physiological noise, and converting to oxygenated hemoglobin concentration (HbO), deoxygenated hemoglobin concentration (HbR), and total hemoglobin concentration (HbT); see Figure 6 for the proposed Homer3 processing pipeline and thresholds for each respective step. These variables can then be used to infer neural activity in brain regions of interest for this task: the motor cortex, which is associated with movement, and the accessible area in the frontal cortex, which is associated with executive functions. These variables are listed in Table S1.

Once the data have been processed, we will assess feasibility based on percentage of usable channels. This will involve taking the number of channels remaining (i.e., those that have not been pruned or otherwise excluded after processing) for each participant, and dividing that number by the total number of channels (i.e., 20). Feasibility will be defined as a participant retaining 60% or more of the possible number of channels (i.e., ≥12 channels).

### 3.2. Motor Performance Results

The Meta Quest Pro Touch Controllers, independent of the Meta Quest Pro Headset itself, use a combination of embedded inertial measurement units (IMUs) and cameras to collect the x, y, and z positional coordinates of the participants’ hands in three-dimensional space. This raw 3D position data will be filtered at 4 Hz using a 2nd order Butterworth filter, a common preprocessing method in studies examining kinematic variables using similar VR systems [63,64]. Once filtered, we can calculate the following kinematic variables as preliminary measures of motor performance. The code, as currently written in Unity, accounts for tracking loss during movement. Any trials with recorded tracking loss will be excluded from analyses.

#### 3.2.1. Reaction Time

Reaction time (RT) is the time between stimulus presentation and movement initiation, measured in milliseconds (ms).RT = Timestamp of Movement Initiation − Timestamp of Stimulus Presentation

To clarify, movement initiation is defined as the moment that the speed of the hand surpasses 0.01 m/s—a threshold that is commonly used to determine movement onset during reaching [62,65]. Accordingly, movement cessation is defined as the moment the speed of the hand is less than 0.01 m/s.

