The traditional gold-standard methods of autism diagnosis and assessment rely on behavioral characteristics, particularly related to social skills and cognitive abilities. The strengths of these assessments are vast and undeniable—they are validated scientific methodologies that are rigorously tested and acknowledged as gold-standard diagnostic measures across both clinical and scientific communities. However, as with all methodologies, limitations remain—for example, the potential for clinician error or bias [26], and a tendency towards missing the female-specific manifestations of autistic traits [27]. Furthermore, commonly used standardized assessments (e.g., Autism Diagnostic Observation Schedule, Autism Diagnostic Interview-Revised) are not intended for use among those with severe motor difficulties or intellectual impairment [26,28]. Therefore, to fully understand the relationships between motor development and other developmental domains, as well as the variability within these relationships, it is crucial to utilize a comprehensive combination of methodologies and assessments. We can gain a variety of outcomes by using a multi-modal approach—in particular, combining these traditional behavioral assessments with methods that can afford various types of physical biomarkers, such as neuroimaging [29]). For example, a combination of standardized motor assessments and movement assessment via 3D motion capture or other similar technologies during research-based tasks can fully assess a child’s motor skill and motor performance via the addition of objective kinematic data [30]. Incorporating neuroimaging can provide further biomarkers of the neural correlates underlying cognitive and motor behavior. For example, a study combining fNIRS with movement tracking during a whole-body sway synchrony task found that autistic children synced less well with a social partner and swayed with smaller amplitude compared to their non-autistic peers [31]. This reduced synchrony was accompanied by lower activity in the superior temporal sulcus and inferior frontal gyrus. Interestingly, when children swayed alone rather than with the adult, the two groups moved similarly. This suggests that the differences only emerged in socially engaged conditions [31]. A related follow-up study used a “reach-to-clean-up” task that combined kinematic and fNIRS recordings across observation, execution, and synchronization conditions in autistic and non-autistic children and found that autistic children showed a greater movement overshoot, speed, and movement segmentation both when moving alone and when synchronizing with an adult, along with reduced prefrontal and temporal activation and higher frontoparietal activation compared to the non-autistic group [32]. fNIRS has also been used with movement-based interventions; in fact, a preliminary randomized control trial used fNIRS to measure cortical activation during a drumming synchrony task before and after eight weeks of creative movement, general movement, or sedentary play interventions in children with ASD, highlighting how fNIRS can serve not only as an assessment tool but as an outcome measure [33]. Together, these studies show that combining brain imaging with movement tracking is a feasible approach for understanding motor and neural profiles of autistic youth and linking brain activity to both movement patterns and intervention response. Even so, this work has stayed narrowly focused on synchrony-based tasks or more specific tasks rather than broader everyday motor skills that are important to target in autistic children. Virtual reality (VR) is another emerging technology being used to assess motor ability [34,35] and conduct motor interventions in autistic youth [36,37]. The overarching work in this growing field, primarily intervention-based, suggests that VR-based interventions are likely feasible and effective in improving motor skills in autistic children [38]. VR has also been successfully used in interventions targeting other developmental domains in autism, such as social and communication skills [39,40,41]. Pairing a custom VR game with low-cost motion tracking, Hocking et al. had ten children and adolescents with autism complete six 20 min VR sessions over two weeks to target their gross motor skills. The authors note that manual motor difficulties in ASD predict adaptive behavior up to 12 years later, underscoring why early motor interventions matter [36]. Another pilot study offers early but meaningful insight into how children and adults with ASD use vision and proprioception in immersive VR. Notably, every participant, including those with higher support needs, readily accepted wearing the head mounted display [42]. Incorporating VR in motor assessment provides real-time measures of human movement and affords movement assessment during a diverse array of research-based VR tasks. These elements are crucial to supplementing standardized movement assessments and producing comprehensive motor profiles in clinical populations.

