#### 3.2.2. Movement Time

Movement time (MT) is the time between movement initiation and movement cessation, i.e., the time elapsed between non-zero velocities throughout a movement—in this case, during reaching towards a target. MT will also be measured in milliseconds.MT = Timestamp of Movement Cessation − Timestamp of Movement Initiation

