#### 3.2.5. Normalized Jerk

Normalized jerk (NJ), a dimensionless measure of variation in acceleration [66], quantifies the smoothness of a movement while accounting for the movement time and length [67]. Small quantities for jerk are indicative of maximum movement smoothness [66]. To calculate normalized jerk, we will use the formula used in Yan et al. (2000) [68], whose calculation methods were originally described by Kitazawa et al. (1993) [69] and Teulings et al. (1997) [70].$$\mathrm{NJ}=\sqrt{(\frac{1}{2})\int j^{2}(t)*({duration}^{5}/{length}^{2})dt}$$

The above equation involves calculating jerk via the derivative of acceleration, then taking the square root of the time integral of squared jerk multiplied by the movement duratation^5^/length^2^.

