**Figure 6 brainsci-16-00947-f006:**
[figure not shown]
The proposed processing pipeline and respective thresholds in Homer3. The thresholds are either standard values in Homer3 or were determined based on previous autism studies using fNIRS [61,62].

**Table 1 brainsci-16-00947-t001:** Research-based task descriptions and cognitive and motor outcome measures.

VR Task: Developmental Domain	Task Description	Brain Region(s) of Interest	Outcome Variables
Cognitive	Go/No-Go task: A Go/No-go paradigm in which participants must “pop” a series of target items—purple balloons—while leaving all blue balloons alone. Balloons will be presented one at a time in randomized locations. Balloon popping will be achieved by a button press on the handheld controller associated with the VR headset (i.e., participants’ hands will remain stationary/in their lap).	Prefrontal cortex Dorsolateral prefrontal cortex	Primary (feasibility-based): Commission Errors (responding to a “no-go” stimulus) fNIRS signal quality
Motor	Reach-and-Pop Balloon Task: Modified version of bubble-popping task in Minissi et al., 2023 [34]; balloons of one color will be presented one at a time at randomized locations and must be popped. The player must reach towards the balloon’s location and then pop the balloon using the button press on the handheld controller. After each balloon, participants must reset their hand to a predefined starting position (under their chin). This will activate the next balloon’s appearance.	Motor Cortex	Primary (feasibility-based): Reaction Time Movement Time Time to Peak Velocity Time to Peak Acceleration Normalized Jerk fNIRS signal quality
Cognitive–Motor	Go/No-Go Reach-and-Pop Task: A combination of the above cognitive and motor tasks, i.e., a Go/No-go Reach-and-Pop paradigm, in which participants must discern between differently colored balloons to reach and pop all purple balloons while blue balloons must be left alone.	Prefrontal cortex Dorsolateral PFC Motor cortex	Primary (feasibility-based): Commission Errors (responding to a “no-go” stimulus) Reaction Time Movement Time Time to Peak Velocity Time to Peak Acceleration Normalized Jerk

**Table 2 brainsci-16-00947-t002:** Primary procedures and outcome measures: feasibility assessment and preliminary behavioral and neural outcomes of research-based tasks.

Consented Individual Involved	Procedure/Assessment	Outcome Measures

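### The reach is ended by a bare 0.01 m/s speed rule with no tie to the balloon or the pop, so a paused reach is cut short and a curved touch-and-return can run into the return leg

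*Protocol article*

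**What the plan says.** Section 3.2.1 fixes both ends of the movement by speed alone: "movement initiation is defined as the moment that the speed of the hand surpasses 0.01 m/s" and, for the end, "movement cessation is defined as the moment the speed of the hand is less than 0.01 m/s". The literature support given there concerns onset; the end rule is carried over from it.

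Section 3.2.2 builds on this: "Movement time (MT) is the time between movement initiation and movement cessation". It also describes the interval as "the time elapsed between non-zero velocities throughout a movement", which is a different criterion from a 0.01 m/s threshold, and gives the intended span as "in this case, during reaching towards a target".

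In Table 1 (Motor row) the child reaches the balloon, presses the button and then goes back: "After each balloon, participants must reset their hand to a predefined starting position (under their chin". No hold at the balloon is required.

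Section 3.2.5 says that NJ "quantifies the smoothness of a movement while accounting for the movement time and length", so it inherits the same end point. Section 3.2 excludes trials only for tracking loss. Section 2.4 records user responses as time-stamped events. Tables 1 and 2 list MT and NJ among the primary, feasibility-based outcomes.

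**The concern.** MT is meant to cover the outward reach, but nothing in the rule says where the hand must be when its speed falls below threshold, or for how long. Two opposite errors follow.

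- **Pause before the balloon.** Speed drops below 0.01 m/s part-way, the window closes, and the rest of the reach is lost. MT and NJ come out too low.
- **No stop at the balloon.** If the hand turns back along a curve, speed may not fall below 0.01 m/s at the turn. The window stays open into the return, and MT and NJ come out too high.

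The error depends on how the child moves, so it is not a constant offset. The first error would hide what NJ is there to detect. The Introduction cites a study in which "autistic children showed a greater movement overshoot, speed, and movement segmentation" than their peers, so segmented reaches are a pattern the authors have reason to expect. Hypothesis 3 asks whether the kinematic data are reliable and valid and change as anticipated, and it would then rest partly on a product of the end rule.

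**Working it through.** The article gives no figure to reproduce, so its rules were applied to constructed reaches.

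**Inputs from the article.** Onset and end threshold 0.01 m/s (3.2.1); 2nd-order Butterworth filter at 4 Hz (3.2); controller rate 1000 Hz and Unity frame rate 90 Hz (2.3), both tried because the article does not say which position record is used; NJ = sqrt(½ ∫j² dt × D⁵/L²) (3.2.5), with D the duration and L the length.

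**Assumptions not in the article.** Minimum-jerk reach of 0.35-0.40 m; 0.8 s unless stated; zero-phase filtering; L as path length; onset as the last upward crossing before the movement and end as the first drop below threshold after it.

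**1. Closed form, unfiltered.** For one minimum-jerk movement ∫j² dt = 720 L²/D⁵, so NJ = sqrt(0.5 × 720) = 18.97, whatever its length or duration. For out-and-back, the integral doubles, D becomes 2D and L becomes 2L: NJ = sqrt(0.5 × 1440 × 2⁵/2²) = 75.9, a factor of 4.

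**2. Pause.** Take 60% of the distance in 0.48 s, a 0.1 s pause, then 40% in 0.32 s.
- Ended at the pause, the first part is itself a minimum-jerk movement, so unfiltered NJ is 18.97.
- Over the whole 0.9 s with L = 0.40 m: ∫j² dt = 720 × (0.24²/0.48⁵ + 0.16²/0.32⁵) = 720 × (2.26 + 7.63) ≈ 7121, and NJ = sqrt(0.5 × 7121 × 0.9⁵/0.40²) ≈ 115.
- With the filter (1000 Hz, 0.40 m): MT 491 ms and NJ 14.7 under the speed rule, against 912 ms and 73.5 to the pop. At 90 Hz: about 500 ms and 15, against about 911-922 ms and 72-75.
- Only about 0.6 × 0.40 = 0.24 m of the reach is counted.
- Pauses of 0.05-0.3 s give MT of about 490-510 ms against 860-1120 ms, and NJ of about 15-16 against 67-119. For a 0.5 s reach, the filter bridges a pause of 0.05 s or less; the cut appears from 0.1 s.

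**3. Touch-and-return with a curved turn (1-3 cm lateral).** At both rates speed stays above 0.01 m/s at the turn. MT is about 1590-1600 ms against 795-800 ms to the pop; NJ is about 60 against 15. The factor of 4 agrees with step 1.

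**4. Touch-and-return on a straight line.** For 800 ms reaches with no overlap of the two legs, 0% merge at either rate. For 600 ms reaches, about 30% merge at 90 Hz and 0% at 1000 Hz. Faster reaches, or legs that overlap in time, raise the 90 Hz share (up to 89% in the cases run); it stays 0% at 1000 Hz.

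**5. Clean stop at the balloon (0.05-0.4 s).** MT is about 790-800 ms and NJ about 15-16, which is correct.

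**6. Ending at the press instead.** With D⁵ under the root, NJ scales as D^2.5 when the hand is still. A 200 ms delay before the press gives a factor of (1000/800)^2.5 = 1.75, so NJ of about 16 becomes about 28; simulation gives 28-29.

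**The case against.** The strongest reply is that the words already confine the window. Section 3.2.2 speaks of reaching towards the target, 3.2.3 places peak velocity within the reach, and 3.2.4 refers to each reaching movement. Dwell time and choice of crossing could sit in the analysis code, and a last-crossing reading would not truncate paused reaches. This stands in part. A reader might infer that time to peak velocity shifts to the return leg; 3.2.3 excludes that in words, so it is not claimed here. But 3.2.1 does more than leave a detail open: it states an operational end rule which, followed as written, can contradict the intended span.

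A reader might also infer that every immediate turn-around doubles MT. That does not hold. The doubling needs a curved turn, or a fast or overlapping straight reversal sampled at 90 Hz. Having to press at the balloon makes a brief stop plausible, and such trials are measured correctly.

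Nor do the documents show a bias between autistic and non-autistic children. The segmentation finding comes from a different task and does not show speed falling below 0.01 m/s. It makes the pause pattern plausible but gives no frequency.

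Finally, these outcomes are descriptive. Section 3 promises descriptive and qualitative results, no test or threshold uses MT or NJ, and windows can be recomputed from stored positions. That lowers the severity, but does not remove the point.

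**Conclusion.** The concern holds as a moderate one. The stated rule can end a paused reach mid-way, with MT roughly halved and NJ about one-fifth of its value to the pop (14.7/73.5 = 0.20). It can also carry a curved touch-and-return into the return leg, with MT doubled and NJ about four times too high. These sizes rest on the assumed minimum-jerk profile, reach length and duration, pause and path shape, zero-phase filter and path-length definition. The documents do not show how often either pattern will occur. They do not support saying that most trials are affected, that the groups are biased apart, or that Hypothesis 3 cannot be assessed. They do support settling the end rule before analysis, since two primary descriptive outcomes depend on it and a later choice would be made after seeing the data.

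**What to change.** In 3.2.1 and 3.2.2, use the pop time-stamp from 2.4 to bound the search, not as the end point itself.

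- Define cessation as the start of the last sub-threshold period, sustained for a stated minimum time and within a stated target zone, that contains or directly precedes the press.
- If speed never falls below threshold there, use the speed minimum nearest the press.
- Ignore earlier pauses, and state a fallback for reaches without a press.
- Compute MT, time to peak velocity, time to peak acceleration and NJ on this one window.
- Replace the non-zero-velocity wording in 3.2.2 with the same definition, and state which sampling rate feeds the speed calculation.

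The cost is two revised definitions, a little more processing code, and a choice of dwell time and target zone. No new data are needed. Ending at the press itself should be avoided, because it would inflate NJ in the clean-stop reaches that the present rule measures correctly.

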#### 3.2.2. Movement Time

Movement time (MT) is the time between movement initiation and movement cessation, i.e., the time elapsed between non-zero velocities throughout a movement—in this case, during reaching towards a target. MT will also be measured in milliseconds.MT = Timestamp of Movement Cessation − Timestamp of Movement Initiation

#### 3.2.3. Time to Peak Velocity

Velocity is the change in position with respect to time, and will be calculated as the first derivative of the position of participants’ hands over the course of each reaching movement. It accounts for movement in both the horizontal and vertical direction, and is thus considered a vector. The time to peak velocity (TTPV), therefore, would be calculated as the total time elapsed between movement initiation and the peak velocity attained during the reach towards the target. TTPV will also be measured in milliseconds.TTPV = Timestamp of Peak Velocity achievement − Timestamp of Movement Initiation

#### 3.2.4. Time to Peak Acceleration

Movement acceleration is the measure of how quickly an object speeds up or changes direction, and will be calculated as the second derivative of the position of participants’ hands over the course of each reaching movement. The time to peak acceleration (TTPA) would be calculated as the amount of time an object takes to reach maximum acceleration after initial movement. TTPA will also be measured in milliseconds.TTPA = Timestamp of Peak Acceleration achievement − Timestamp of Movement Initiation

#### 3.2.5. Normalized Jerk

Normalized jerk (NJ), a dimensionless measure of variation in acceleration [66], quantifies the smoothness of a movement while accounting for the movement time and length [67]. Small quantities for jerk are indicative of maximum movement smoothness [66]. To calculate normalized jerk, we will use the formula used in Yan et al. (2000) [68], whose calculation methods were originally described by Kitazawa et al. (1993) [69] and Teulings et al. (1997) [70].$$\mathrm{NJ}=\sqrt{(\frac{1}{2})\int j^{2}(t)*({duration}^{5}/{length}^{2})dt}$$

The above equation involves calculating jerk via the derivative of acceleration, then taking the square root of the time integral of squared jerk multiplied by the movement duratation^5^/length^2^.

## 4. Discussion

The above proposed methods have strong potential to yield a rich combination of kinematic, cognitive, and neural data. The use of neuroimaging during research-based tasks is crucial to expanding our understanding of autistic brain dynamics underlying cognitive–motor task performance. Furthermore, the use of neuroimaging and VR present individual and combined supplemental contributions to autism assessment methods. These assessments are invaluable and irreplaceable in the diagnostic sense—however, typical assessment and diagnostic measures, which rely on observational measures of behavior, can potentially be supplemented and augmented through the data yielded via technology such as fNIRS and VR. These methods also lay the groundwork for developing new, multifaceted interventions that can be tailored to individual support needs. VR, an already emerging means of intervention and support in autism research, has strong potential to address individual needs across the spectrum due to its inherently adaptable nature. The addition of neuroimaging provides more individualized data underlying task performance in the VR environment, offering the potential to tailor VR tasks to autistic brains across the spectrum.

We would be remiss to not mention the limitations of our design. Although fNIRS and VR have been individually well-tolerated in autistic youth, we must also consider the sensory aspect of combining these measures. It may be overwhelming to participants to have both apparatuses on their heads simultaneously—a hallmark of why beginning our work with feasibility assessments is crucial to move forward with the project as a whole. VR also poses the risk of cybersickness, which, like motion sickness, can cause symptoms such as nausea, disorientation, and visual discomfort. VR has been used previously in autism research with great success—nonetheless, our researchers will continuously check in with participants during the VR tasks and prioritize their comfort and well-being.

Furthermore, our current research-based task design can be considered limiting in and of itself. One task with various conditions/manipulations of cognitive and motor domains certainly cannot generalize to assessing cognitive and motor development at large, particularly considering the developmental heterogeneity among autistic youth. The behavioral and neural responses elicited will be specific to the task selected, and future work using additional tasks alongside this proposed task paradigm is needed for more comprehensive developmental assessment. Standardized assessments will also be crucial to this larger, holistic understanding of developmental domains in autism. These assessments, which are further detailed in the Supplementary Materials, target cognitive (e.g., Behavior Rating inventory of Executive Function—2nd edition (BRIEF-2)), motor (e.g., Bruininks-Oseretsky Test of Motor Proficiency—3rd edition (BOT-3)—Fine Motor Portion, and social and emotional development (e.g., Social Skills Improvement System (SSIS) Rating Scales). Once the feasibility of combining neuroimaging and virtual reality in autistic youth has been established, integrating the results of these standardized measures will afford the opportunity for validating our behavioral data, as well as allow us to examine the interrelationships between clinical profiles and cognitive and motor task performance.

This feasibility study and the preliminary cognitive and motor data gathered will set the groundwork for a multitude of future studies assessing the interrelationships between cognitive, motor, and social development in autistic children. Our preliminary, simplistic research-based task design sets the stage for creating much more complex tasks across various developmental domains, with VR affording malleable, controllable, and extremely realistic environments. We hope by combining neuroimaging and virtual reality paradigms, we can use these methods in addition to traditional assessments, such as the ADOS. Furthermore, in the long-term, this work will advance multi-modal, holistic, and comprehensive autism research—viewing these relationships and their neural correlates through a multifaceted lens will inform our understanding of the autistic brain, diversify autism assessment methods, and improve intervention strategies across the autism spectrum.

